### Measures

Educators (principals/administrators, teachers, paraeducators) will complete secure web-based surveys via REDCap at three time points (Table 1). Time points will be baseline (April/May; T1) before the academic year in which schools will receive HELM, winter (Jan/Feb; T2, 8–9 months after baseline), and spring of the subsequent year (April/May; T3, 12 months after baseline). Educators will self-report their demographic characteristics, organizational mechanisms of change (implementation leadership and climate), implementation time and costs, and deidentified classroom-level outcomes. Educators will be compensated $40 for the completion of study instruments at each data collection timepoint.

**Table 1 Tab1:** Study Measures

Construct	Measure Description	Source	Time
School demographics	School size, student body racial/ethnic composition, % free/reduced lunch	A	T1

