	**Implementation Outcomes**		
PBIS Fidelity	The *Tiered Fidelity Inventory* (TFI; [54]) is a 45-item tool used to provide a valid, reliable, and efficient measure of the extent to which school personnel are applying the core features of PBIS. The TFI is a group-assessment completed by a schoolwide system planning team with external facilitation with strong internal consistency (α = .96). The TFI will be collected for both PBIS + HELM and PBIS + IAU conditions across the three time points	P DLT T O	T1-T3
Implementation Cost	Costs of 1) delivering HELM to augment PBIS implementation, as well as 2) IAU, will be calculated using activity-based cost metrics. Inputs will include time, supplies, travel, overhead, and costs associated with HELM training/coaching meetings, including pre-work, scheduling, and attending meetings; as well as costs associated with PBIS training and delivery in each study condition.	A P DLT T	T1-T3

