	**HELM Manipulation Check**		
HELM Fidelity	Coding of video recordings of HELM delivery	O	T1 -T3

Note: *A* Administrative data, *P* Principal, *DLT* distributed leadership team, *T* Teacher, *O* Trained observer; T1 = Baseline (Apr/May prior to HELM/PBIS delivery year), T2 = Jan/Feb, 9 months after baseline, T3 = Apr/May, 12 months after baseline

*Fidelity*. The study’s primary outcome is school-level PBIS fidelity, assessed using the Tiered Fidelity Inventory (TFI; [54]). Facilitated by an expert PBIS coach, school PBIS implementation teams will complete the TFI in both the HELM and control conditions. The TFI is designed to be used 1) for initial assessment to determine the degree to which a school is using PBIS-consistent practices; 2) as a guide for implementation of Tiers 1, 2, and 3 EBPs, and 3) to track PBIS implementation over time. TFI data will be collected at the same time points as educator data.

*HELM fidelity checklist*. This checklist will be used as a manipulation check to document HELM delivery (based on observations of recorded HELM trainings). HELM coaches will complete a standardized measure of dates specific steps were completed.

*Qualitative Focus Groups*. We will develop a systematic, comprehensive semi-structured focus group guide that draws from the EPIS framework to examine multilevel (i.e., intervention, individual, inner, and outer settings) determinants that explain what processes facilitated or hindered implementation [28]. We will generate questions that explore the most salient implementation determinants and mechanisms, and how implementation leadership and climate may interact with other relevant characteristics of the setting [57, 58].

*Administrative Data*. At the end of each school year, deidentified academic records by classroom will be requested for all participating schools to extract students’ attendance, discipline (office disciplinary referrals), and achievement (grades, standardized test scores). To assist in modeling, these data will be collected retrospectively for the year prior to HELM participation as well as each cohort’s HELM year.

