*Cost Assessments*. Activity-based costing will be used to comprehensively estimate the costs of HELM and the comparison condition [59, 60]. We will measure cost from the payor (i.e., school system) perspective, since the primary costs and associated decision-making are within the implementing school district [61]. We will isolate costs of HELM as an implementation strategy, but since HELM may have secondary impacts on PBIS costs – e.g., by increasing educator engagement in implementation – we will measure and monetize differences between study conditions in costs related to teachers’ participation in PBIS training, consultation, and delivery.

We will include open-ended items in each survey that ask about unexpected resources needed for HELM and/or PBIS. Using a sequential qual → QUANT development function, we will rapidly analyze responses on an ongoing basis so that we can immediately incorporate any newly identified cost categories into future surveys for quantitative measurement [62, 63]. To assign cost values to categories that are measured in non-monetary values (e.g., trainer time delivering HELM, teacher time spent on PBIS), we will use other data sources such as school district records or project expense reports.

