*Qualitative Analysis.* Certain codes will be conceptualized during the protocol guide development and driven by the EPIS framework (i.e., deductive approach) and others will be developed through reading an initial subset of transcripts (i.e., inductive approach). Themes will provide a way of understanding the most salient factors that impact implementation and extend beyond the existing HELM organizational mechanisms and theory of change [79, 80]. EPIS-driven directed coding will include system levels (i.e., intervention, individual, inner setting, outer setting) as initial “parent nodes.” After a stable set of codes is developed, a consensus process will be used in which all reviewers independently code and compare their coding to arrive at consensus judgments through open dialogue [81–83].

*Cost and Cost-Effectiveness Analyses*. We will use the CostOut program to complete the cost analysis for HELM and PBIS implementation-as-usual. CostOut specifies ingredients for each intervention condition, assigns prices (national and user-inputted local values), and calculates costs based on the units per ingredient used [59, 84]. We will use CostOut to generate descriptive statistics describing typical costs (i.e., means, standard deviations) for HELM and PBIS. We will calculate total costs for each condition, and incremental costs of HELM over PBIS training and technical assistance only. We also will provide cost breakdowns to help administrators understand the budget implications of HELM, including personnel versus other direct expenses and start-up versus maintenance costs. Finally, we will conduct sensitivity analyses to examine the robustness of our cost estimates by identifying areas of uncertainty in measuring the units and prices for our ingredients, and then calculating costs across a range of plausible values [85, 86].

We also will use CostOut to calculate the cost-effectiveness of HELM versus PBIS [87]. This will involve calculating a series of incremental cost-effectiveness ratios for each student outcome (social, emotional, behavioral, academics) and PBIS implementation outcome (fidelity). Finally, we will again use sensitivity analyses to examine the robustness of our cost-effectiveness results, both across the ranges of costs examined and across plausible effectiveness estimates (i.e., 95% CIs for student and implementation outcomes).

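### PBIS costs are collected at baseline, but the described cost comparison does not use them; adjusting for T1 cost would sharpen the PBIS part of HELM's incremental cost (optional)

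*Protocol article*

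**What the plan says.** **What is costed.** The Implementation Cost row of Table 1 (Measures) reads: "Costs of 1) delivering HELM to augment PBIS implementation, as well as 2) IAU, will be calculated using activity-based cost metrics". The inputs include HELM activities "as well as costs associated with PBIS training and delivery in each study condition". The row is scheduled for T1 to T3.

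**When.** The opening paragraph of Measures lists what educators self-report in the three surveys, including "organizational mechanisms of change (implementation leadership and climate), implementation time and costs, and deidentified classroom-level outcomes". The Table 1 note defines the first wave: "T1 = Baseline (Apr/May prior to HELM/PBIS delivery year", that is, before either programme is delivered under the trial.

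**What counts towards HELM.** Cost Assessments (Measures) isolates HELM's own costs. Because HELM may also change spending on PBIS, it adds: "we will measure and monetize differences between study conditions in costs related to teachers’ participation in PBIS training, consultation, and delivery".

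**How the difference is obtained.** Cost and Cost-Effectiveness Analyses (Data analysis) uses CostOut, which assigns prices and "calculates costs based on the units per ingredient used". Means and standard deviations are reported, then "We will calculate total costs for each condition, and incremental costs of HELM over PBIS training and technical assistance only". Cost-effectiveness ratios follow for each student outcome and for fidelity. Sensitivity analyses vary units and prices, and for the ratios also the effect estimates across their 95% intervals.

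**The concern.** PBIS effort at T1 cannot be an effect of HELM. It is a pre-randomized-period measure of the same quantity that is later compared between arms, which makes it a natural baseline covariate. Schools are also expected to differ at entry: districts qualify either through PBIS training in the past two years or through willingness to train at the outset (Participants), and Limitations expects variable PBIS implementation.

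The cost section sets out its steps, and none of them uses T1 cost as a baseline. The covariate rules in Data Analytic Approach are written for models, whereas the described cost step is unit-times-price arithmetic. Effects in the cost-effectiveness ratios would thus come from covariate-adjusted models, while the PBIS cost difference in the same ratios would be a raw contrast of 21 schools with 21.

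At stake is precision. Chance differences between arms in PBIS effort that predate HELM carry forward into the T2-T3 PBIS cost difference, and from there into the numerator of each ratio.

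**Working it through.** The article states no cost, cost SD, incremental cost or cost-effectiveness ratio, so there is no figure of its own to reproduce. The check is of relative precision only.

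**Inputs**
- 42 schools, 21 per arm (Abstract; Participants).
- Cost waves T1, T2 and T3, with T1 before the delivery year (Table 1 and its note).
- Correlation r between a school's PBIS costs at any two waves: not given. I assume a range of 0.3 to 0.8. The value 0.71 = √0.5 is borrowed from Power Analysis, where pretests explain 50% of posttest variance. That figure is stated for trial outcomes, not costs.
- Equal school-level variance σ² at each wave: assumed.

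**Formulas**
- Unadjusted post-baseline total: Var(T2+T3) = σ²(2 + 2r).
- Covariance with baseline: Cov(T2+T3, T1) = 2rσ².
- Adjusted for T1: Var(T2+T3 | T1) = σ²(2 + 2r − 4r²).
- SE of the arm difference = √(variance × 2/21).
- SE ratio, adjusted to unadjusted = √[(2 + 2r − 4r²)/(2 + 2r)].

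**Results** (SE in units of the per-wave SD)

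| r | Var, unadjusted | Var, adjusted | SE, unadjusted | SE, adjusted | Ratio | Reduction |
|---|---|---|---|---|---|---|
| 0.3 | 2.60 | 2.24 | 0.50 | 0.46 | 0.93 | 7% |
| 0.5 | 3.00 | 2.00 | 0.54 | 0.44 | 0.82 | 18% |
| 0.71 | 3.41 | 1.41 | 0.57 | 0.37 | 0.64 | 36% |
| 0.8 | 3.60 | 1.04 | 0.59 | 0.32 | 0.54 | 46% |

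These are large-sample figures. They ignore the small loss from estimating the slope on T1 from 42 schools, so at r = 0.3 little is gained.

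**Baseline imbalance.** Under simple randomization, the SE of the T1 difference is √(2/21) = 0.31 SD, and a difference above 0.25 SD has a 42% chance. This trial does not use simple randomization, so those figures overstate the position. If constraining on prior PBIS implementation and school size removes 25%, 50% or 75% of T1 cost variance (assumed), the chance falls to about 35%, 25% or 10%. An imbalance of 0.25 SD that did occur would shift the unadjusted T2+T3 difference by 0.25 × 2r: 0.15 SD at r = 0.3 and 0.35 SD at r = 0.71.

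**The case against.** The best case against is that this is a condensed article. How costs are adjusted is a detail that a fuller plan may hold, and the article nowhere calls the increment unadjusted. A descriptive ingredients costing is also a coherent choice for an exploratory question (Aim 2, Research Question 2e). The randomization already constrains prior PBIS implementation and school size, two plausible drivers of baseline PBIS cost. Data Analytic Approach also provides for adjustment for non-equivalent baseline characteristics, and the article does not exclude costs from that rule. Finally, the size of the gain depends on an assumed correlation.

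Most of this stands, and it limits the point to an optional improvement. It does not remove it: the cost steps that are described leave no place for a covariate, and constraining on fidelity and school size is not the same as using the measured T1 cost.

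A reader might go further and infer from the T1-T3 label that baseline costs are summed into the condition totals, which would add pre-HELM noise directly to the increment. The documents do not support this. Table 1 also lists HELM fidelity at T1-T3, although HELM has not begun at T1, so the column reads as a general measurement schedule. The cost section specifies ingredients by intervention condition and does not say which waves are added. I make no claim that T1 is included.

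**Conclusion.** T1 PBIS cost is collected, and the cost analysis as described does not use it as a baseline. The consequence is lost precision in the PBIS-related part of the increment: an avoidable share of the standard error of about 7% to 46% over r = 0.3 to 0.8, before subtracting what the constrained randomization covariates already capture. This rests on equal variance per wave and a common correlation between waves, neither of which the article gives for costs.

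A reader might also infer that HELM's incremental cost is biased, or that its sign could merely reflect pre-trial activity. Neither follows. Randomization makes the imbalance a matter of chance, HELM's own delivery costs are isolated and unaffected, and no figure in the article shows how large the PBIS part is relative to the whole. This is an optional gain for Research Question 2e, not an error in the plan.

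**What to change.** Keep CostOut for pricing ingredients and for the descriptive costs. For the between-arm comparison:

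1. Compute each school's PBIS cost over T2-T3, and separately its T1 PBIS cost.
2. Regress the T2-T3 cost on condition, T1 PBIS cost and the randomization covariates, with the school as the unit. T1 cost enters as a covariate and not as part of the total. Fit on the money scale, so that the coefficient for condition is a cost difference.
3. Add the isolated HELM cost to that adjusted difference and use the sum as the numerator of the cost-effectiveness ratios.

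The price is one extra school-level regression run outside CostOut, with no new data. The article reports no enrolment as of February 2025, so at that date the step could still be prespecified.

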## Discussion

One out of 5 elementary students exhibit social, emotional, and behavioral difficulties that hinder their academic success which are linked to later negative outcomes, including substance use problems, unemployment, houselessness, and contact with the legal system [1, 88, 89]. Despite the promise of EBPs like PBIS to promote student social, emotional, and behavioral functioning, their routine use in schools is limited, reducing their large-scale impact on student outcomes [90, 91]. The majority of schools in the United States are attempting to implement multi-tiered frameworks such as PBIS, yet evidence suggests that implementation in educational settings is typically absent, inconsistent, or incomplete [91, 92]. School leadership plays a pivotal role in the successful implementation of EBPs that effectively reduce social, emotional, and behavioral outcomes [13, 93]. The presence or absence of strong leadership support in schools can make the difference between successful implementation and abandonment. However, leadership is not specifically targeted in standard PBIS training [93].

Research on leadership-focused implementation strategies have almost exclusively focused on outpatient mental health clinics or clinics focused on treating substance use disorder [25–27, 27–31] and has not been widely evaluated in public schools. There is some preliminary evidence to suggest HELM positively impacts implementation leadership, implementation climate, and implementation citizenship and may potentially buffer the decline in EBP implementation efforts that naturally occurs over the school year [94]. This study will be the first full-scale test of HELM’s efficacy in public schools, which is a very different service setting with unique organizational characteristics, systems, and processes. It is important to test whether the type of leadership-focused training and climate development that worked in outpatient mental health clinics or clinics focused on treating substance use disorder also can work in public schools.

HELM has the potential to reduce the substantial waste in time and resources resulting from ineffective universal EBP implementation, including inadequate uptake and low fidelity. HELM is closely aligned with the needs and priorities of educators working in educational settings due to its applied focus and emphasis on strategic implementation behaviors. Demonstrating the effectiveness of HELM on PBIS fidelity will address a highly prevalent barrier to improved population health: abandonment or low-fidelity delivery of effective interventions focusing on social, emotional, and behavioral functioning in schools. Because HELM was developed and tested with school partners, it has the potential to be highly usable and scalable, which has significant implications for low-resource community contexts in which lay providers deliver services. A unique aspect of HELM is that it emphasizes the engagement of DLT in schools, which is a common leadership model in schools but not in outpatient mental health clinics or clinics focused on treating substance use disorder. As of February 2025, no participants have been enrolled.

### Limitations

We recognize that it will be difficult to identify school districts that have not engaged in some level of PBIS implementation. However, for maximum generalizability and educational impact, HELM needs to be able to support both initial implementation of an EBP as well as improve implementation efforts that are already in process. Schools with variable levels of PBIS implementation will allow us to examine this effect.

## Data Availability

The application described in this manuscript is freely available. Please contact the lead author for more information.

## Abbreviations

CWIS: Cognitive Walkthrough for Implementation Strategies
DBR: Direct Behavior Ratings
DDBT: Discover, Design/Build, Test
DLT: Distributed Leadership Teams
EBP: Evidence-based practice
EPIS: Exploration, Preparation, Implementation, Sustainment
ES: Effect Sizes
HELM: Helping Educational Leaders Mobilize Evidence
ICBS: Implementation Citizenship Behavior Scale
IES: Institute of Education Sciences
LOCI: Leadership and Organizational Change for Implementation
MBI-ES: Maslach Burnout Inventory – Educators Survey
MDES: Minimum Detectable Effect Sizes
ML-PA: Multilevel path analysis
MLR: Maximum likelihood estimator
PASS: Power Analysis and Sample Size Software
PBIS: Positive Behavioral Interventions and Supports
REDCap: Research Electronic Data Capture
TFI: Tiered Fidelity Inventory
TPS: Team Process Scale
